### Participants

A total sample of 116 healthy expectant mothers will be recruited during pregnancy in the region of the Radboud University, The Netherlands. In this region, 17.800 children are born every year [48]. Pregnant women have to meet the following eligibility criteria: age ≥ 18, singleton pregnancy, no drug use during pregnancy, no severe physical or mental health problems, and sufficient understanding of the Dutch language. Also, exclusive participation in this intervention trial is required. The infants have to be born at ≥37 weeks of pregnancy and have to meet the following eligibility criteria: no congenital anomalies, birth weight ≥ 2500 g, and 5-min Apgar score ≥ 7. The participant flow is displayed in Fig. 1.

**Fig. 1 Fig1:**
[figure not shown]
Participant flow

### Outcomes

Tables 1 and 2 show the maternal and infant primary and secondary outcomes at the different time points. Table 3 shows the additional information, such as the demographics and confounders that will be collected in the current study.

**Table 1 Tab1:** Maternal outcome measures

Construct	Timing (W = week/Y = Year)				Measure	Additional information
	W2	W5	W12	Y1		
Primary outcome						
1. Mental health						
1.1 Depressive symptoms	x	x	x	x	Edinburgh Postnatal Depression Scale (EPDS)	10-item validated questionnaire to screen for depressive symptoms in a post-partum setting [53].
Secondary outcomes						
1. Mental health						
1.2 Anxiety	x	x	x	x	State-Trait Anxiety Inventory (STAI)	The STAI is a 40-item validated questionnaire to screen for anxiety [54].
1.3 Stress	x	x	x	x	Alledaagse Problemen Lijst (APL)	The APL is a 49-item validated questionnaire to assess the occurrence and intensity of daily hassles [55].
1.4 Traumatic Stress following child birth	x	x	x	x	Traumatic Event Scale-B (TES-B)	The TES-B is a 35-item validated questionnaire to examine traumatic stress after giving birth to a child [56].
1.5 Sleep quality	x	x	x	x	Adjusted version of the Karolinska Sleep Diary (KSD) & Pittsburgh Sleep Quality Index (PSQI)	Every morning, for three consecutive days, the mother will fill in the KSD starting at week two, five and twelve [57]. In addition, questions related to daytime sleep and reasons for wakening will be included. At twelve weeks and one year, the mother will fill in de PSQI [58]. The PSQI is a 19-item validated questionnaire to examine sleep quality and disturbances in reference to their sleep during the past month.
2. Physical health						
2.1 Physical recovery related to the delivery	x	x	x	x	Maternity carer logbook & Multidimensional Fatigue Inventory (MFI) & Bodily Pain subscale of the Short-Form Health Survey (SF-36)	The maternal physical recovery logbook of the maternity carer from the first week after birth will be copied at the second home visit. The MFI is a 20-item validated questionnaire to examine fatigue [59]. The two-item subscale of the SF-36 will be used to examine bodily pain [60].
2.2 Health		x	x	x	Health interview & questionnaire	A maternal health interview, based on the infant health interview [61], will be performed during the second home visit. During the follow-up assessment the mother will fill out health questionnaires, based on the infant health interview [61].
2.3 Breastfeeding	x(w1–12)			x	Weekly logbook	The mother will fill out a weekly logbook including the estimated times of breastfeeding, expressed breastmilk feeding, and formula feeding to examine breastmilk initiation, exclusivity, frequency and duration. At one year of age, mothers will note the number of months the infant was breastfed and she will note the current feeding status.
2.4 Physiological stress		x			Hair cortisol	Hair analyses will be used to show the activity of the HPA axis over longer periods of time. A strand of hair will be cut from the scalp.
3. Mother-infant relationship						
3.1 Mother-infant bond	x	x	x	x	Maternal Postnatal Attachment Scale (MPAS)	The MPAS is a 19-item validated questionnaire to assess current maternal attitudes, thoughts, and feelings towards the child [62].
3.2 Quality of maternal caregiving behavior (sensitivity)		x			Ainsworth Sensitivity Scales	An infant bathing session during the home visit on week five will be videotaped. After, reliable observers, blinded for group allocation, will observe maternal sensitivity [63].
3.3 Quality of maternal caregiving behavior (synchrony)		x			Saliva cortisol	Synchrony will be measured with saliva samples of both the mother and infant before and after the bathing session (undressing, bathing and dressing). Samples will be collected right before undressing (baseline, T1), and 25 (stress, T2) and 40 (recovery, T3) minutes after the infant is taken out of bath [64]. Saliva will be collected in tubes for the mother and with eye sponges for the child [65]. Cortisol synchrony consists of the within mother-infant dyad cortisol associations (i.e. mother cortisol predicting infant cortisol, infant cortisol predicting mother cortisol). Cortisol synchrony will be examined for every saliva sample (pre-stress, peak-stress, recovery), for total stress cortisol concentrations (Area Under the Curve (AUC)), and cortisol recovery (recovery – pre-stress).
Secondary outcomes: Underlying mechanism						
Oxytocin concentrations		x			Saliva oxytocin	Maternal oxytocin concentrations during the bathing session will be measured in saliva at the same time points as cortisol. Saliva will be collected in tubes.

**Table 2 Tab2:** Infant outcome measures

Construct	Timing (W = week/Y = Year)				Measure	Additional information
	W2	W5	W12	Y1		
Secondary outcomes						
1. Behavior						
1.1 Crying and fussing	x	x	x		72-h study diary	Crying and fussing will be collected with a simply designed 72-h logbook that mothers fill in with lines [66].
1.2 Sleep quality	x	x	x	x	72-h study diary & Adjusted version Brief Infant Sleep Questionnaire (BISQ)	Mother will note the amount of sleep time in the crying and fussing diary at week two, week five, and week twelve [66]. Additionally, the mothers will complete the infant sleep-screening tool in reference to their child’s sleep during the past week at week two, week five, week twelve and year one [67].
2. Physical health						
2.1 Growth & health		x	x	x	Well-baby clinic logbook & Health interview and questionnaires	Growth and weight information will be copied from the well-baby clinic logbook at week 12 and year one. In addition, a health interview will be performed during the second home visit [61]. Also, the mother will fill in health questionnaires, based on the infant health interview, at week 12 and at 1 year of age [61].
2.2 Physiological stress		x			Saliva cortisol	Infant cortisol reactivity and recovery will be measured with the saliva samples of the infant during the bathing session [64].
3. General development						
3.1 Regulation capacities			x	x	Infant Behaviour Questionnaire Revised (IBQ) – Short form	The IBQ is a 91-item questionnaire to assess infant regulation capacities with the Orienting/Regulation subscale [68].
3.2 Language, cognitive and motor capacities				x	Ages and Stages Questionnaire- Third edition (ASQ-3)	The ASQ-3 is a 30-item validated questionnaire to assess communication, gross motor, fine motor, and adaptive problem solving skills [69]. The Personal-Social subscale of the ASQ will be used as a measure for social-emotional capacities (see 3.3).
3.3 Social-Emotional capacities				x	Brief Infant Toddler Social Emotional Assessment (BITSEA)	The BITSEA is a 42-item validated questionnaire to examine social and emotional behavior such as externalizing and internalizing behavior [70]. The Personal-Social subscale of the ASQ will be used (see 3.2) [69].
Secondary outcomes-Underlying mechanism						
Intestinal microbiota	x	x		x	Stool samples	Stool will be collected from the diaper by the parents. Stool will be collected in tubes.

**Table 3 Tab3:** Additional information

Measure	Timing (P = late pregnancy/W = week/Y = Year)					Details
	P	W2	W5	W12	Y1	
Eligibility criteria						
Medical checklist	x					During the telephone call in pregnancy the medical checklist will be filled out to examine severe physical and mental health problems. In addition, eligibility questions will be answered: age, language proficiency, singleton versus twin pregnancy.
Self-developed delivery questionnaire		x				Infant weight, Apgar, birth and delivery complications, born ≥37 weeks of pregnancy
Demographics						
Demographics questionnaire	x					Maternal age, educational level, SES, drugs use, alcohol use, smoking, number of siblings, age of siblings.
Self-developed delivery questionnaire		x				Infant sex.
Physical contact						
Daily logbook/weekly logbook/questionnaire on physical contact		x(w1–12)			x	Mothers will register 1) holding, 2) SSC, and 3) no contact, as three distinct behavioural categories, for every 15 min with simple lines for the first 5 weeks after birth. In the daily logbook, mothers are able to discriminate between holding and SSC by the mother or other caregivers. Between week 5 and week 12, all mothers will note the estimated time spent in daily holding and SSC on a weekly basis. During the follow-up assessment at 1 year after birth, mothers will indicate how many weeks after week 12 they provided SSC to their infant.
SSC protocol adherence						
Maternal prenatal depressive symptoms, anxiety, and stress	x					The EPDS to screen for depressive symptoms [53]. The Pregnancy-Related Anxieties Questionnaire-Revised (PRAQ-R) is a 34-items validated questionnaire to screen for pregnancy related anxieties [71]. The STAI to screen for anxiety [54]. The Pregnancy Experience Scale (PES) is a 43-items validated questionnaire to assess perceived maternal appraisal of pregnancy-related daily hassles [72]. A 20-item self-developed questionnaire to examine worries related to the preparation for the baby’s arrival. The APL to screen for the occurrence and intensity of daily hassles [55].
Mother-infant bond	x					The Maternal Antenatal Attachment Scale (MAAS) is a 19-item validated questionnaire to assess maternal attitudes, thoughts, and feelings towards the unborn child [73].
Self-developed delivery questionnaire		x				Number of days the father stayed at home after birth.
Weekly logbook sleep location & night awakenings		x(w1–12)				The mother will register the primary sleep location of the infant during 00.00–05.00 h for the previous week [47, 74]. Also, the average number of night awakenings of the infant between 00.00–05.00 h will be noted in the weekly logbook.
Parental ethnographies questionnaire	x		x			10-item questionnaire to assess cultural conceptions on parenting [75].
Social support questionnaire	x		x			Adjusted version of the Social Support Effectiveness Questionnaire (SSE-Q) to examine instrumental, informative and emotional partner support, and negative affect [76].
Social touch			x			The Social Touch Questionnaire (STQ) is a 20-item questionnaire to assess attitudes towards social touch [77].
Adult attachment			x			The Experiences in Close Relationships Scale (ECR) is a validated 36-item questionnaire to asses adult attachment to her current and previous partners [78].

### Study protocol

See Table 4 and Fig. 2 for details of the study procedure.

**Table 4 Tab4:**
[figure not shown]
Enrolment and intervention schedule

**Fig. 2 Fig2:**
[figure not shown]
Study procedure

### Recruitment

The recruitment includes a cover story. Mothers will be told that the study will focus on the relationships between infant sleep and feeding behavior, mother-infant contact, and maternal and infant mental and physical health. In addition, the mothers will be told that a subgroup of the pregnant women will be asked to implement a natural and simple 5-week daily contact period with their newborn infant, starting immediately after birth.

Women will be recruited from a database of pregnant women who have expressed their interest for participating in scientific research. In addition, the experimenter will recruit women at pregnancy clubs, baby fairs, and baby shops. All expectant women will be informed about the study with the study flyer and study website.

After signing up, all expectant mothers will be telephoned by the principle investigator to provide more information about the study. The eligibility questionnaire will assess the eligibility of the mother. Next, a home visit in late pregnancy (week 34–36) will be arranged for interested and eligible women to explain the study in person by the principle investigator.

### Randomization

Primiparous mothers are expected to have more opportunities to provide SSC to their infants compared to multiparous mothers. A stratified random block randomization method will ensure a balance between the SSC and the control condition for the primiparae versus multiparae mothers. Also, this randomization method produces comparable groups by avoiding confounding from known and unknown factors [49]. The block sizes will be randomly chosen from the set of 4 and 6. Randomization will be with a 1:1 allocation. An independent researcher, who is not involved in the study, will prepare this schedule by a computerized randomisation program and will conceal the allocation sequence in stapled envelopes. The allocation sequence will be concealed from the researcher enrolling and assessing participants. The mothers will be included in the study after signing the informed consent, regarding the use of participant data and biological samples (see Additional file 3 for the Dutch versions of the informed consent form and information statement for participants), and filling out the medical checklist during the pregnancy home visit. Hereafter, the principal investigator will open the envelope and the mothers in the SSC group will be informed about their group allocation. Participants and the principle investigator will not be blinded for the group allocation.

### Intervention and control condition

The study of Bigelow and colleagues requested their mothers to provide at least 6 h of SSC per day in the first week after birth and continue with at least 2 h of SSC per day until the infant was one moth of age [15]. However, many mothers did not meet the SSC criterion. In this study we reduce the amount of requested hours and extend the number of requested weeks of daily SSC to enlarge the number of mothers that meet the SSC criterion. In the Netherlands mothers are entitled to at least 10 weeks of paid maternity leave after delivery, which will facilitate adherence to our adapted SSC protocol. During the instruction phase of the pregnancy home visit, all mothers in the intervention group will be provided with detailed written and oral instructions on SSC. We will request and encourage mothers in the SSC condition to provide their infants with at least one uninterrupted hour of maternal SSC, on a daily basis and for 5 weeks, starting immediately after birth. Other caregivers are allowed to provide supplementary hours of SSC to the infant. The period of one uninterrupted hour is based on two arguments. First, the average duration of the sleep cycle of healthy full-term infants is 47 min [50]. The requested uninterrupted hour decreases the chance that infants need to be disturbed in the middle of a sleep cycle. Second, shorter SSC episodes could potentially decrease or eliminate the effectiveness of SSC, since undressing and dressing can be defined as a mild physical stressor for infants [51]. The requested uninterrupted hour requires to undress and dress the infant only once. During SSC, the naked infant, wearing only a diaper, will be placed in a stable and upright position between the breasts of the mother to facilitate and maximize SSC. The head of the infant is positioned in a slightly upright position to keep the airway open. After, the infant and mother will be covered by a blanket or cardigan (see also the practical guidelines of the World Health Organization [11]). Mothers in the SSC condition will explicitly be asked to feed their child before SSC. However, we will not discourage breastfeeding during SSC. During the oral and written instructions, we will explain safety precautions during SSC. We will emphasize the importance of being awake and alert during SSC, and of avoiding drinking hot beverages during SSC to protect the infant. During the second home visit (week 5 after birth), we will ask mothers whether they experienced problems with the safety precautions. Mothers in the control condition will not be requested and encouraged to provide SSC to their infant.

Mother in both groups will fill out the same daily contact logbook. In the daily logbook, all mothers will be asked to register for every 15 min with simple lines the following three categories: 1) holding, 2) SSC, and 3) no contact. In this logbook, mothers are also able to discriminate between holding and SSC by the mother or other caregivers, for example the father or grandparents.

Upon signing the informed consent, participants are informed that they may decide to discontinue the study at any moment and without giving a reason. Several measures are taken in order to minimize attrition and maintain adherence to the study. During the 5-week trial period, the principal investigator will have weekly contact with the participating mothers. Participants will be reminded of the upcoming data collection and they will be asked about any problems they are having with skin-to-skin contact, in filling out the logbooks, or with the collection of the stool samples. In addition, to improve participant retention the mothers will receive a small present after birth, and a present and a financial reimbursement of 20 euros at the home visit in week 5. Last, the mothers will receive the study-wide results after publication of the study reports.

### Pregnancy home visit

One day before the pregnancy home visit, an e-mail will confirm the home visit. During this visit, the researcher reconfirms eligibility. Based on the cover story, the experimenter will provide additional information about the study. If mothers are still interested, informed consent is obtained by the principle investigator and mothers will fill out the medical checklist. Next, the SSC group will be informed about the group allocation. Expectant mothers in the SSC group will receive detailed instructions on SSC. All expectant mothers will receive the information statement with a summary of the instructions about the prenatal and postnatal part of the study. Also, the experimenter will explain how the study logbooks and questionnaires need to be filled out, and how the samples need to be collected. Additionally, the mother will be asked about her preference related to the communication during the intervention period (e-mail versus text-message). Lastly, the mother will fill out the prenatal questionnaires.

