## Methods

### Study design

This SSC intervention project in mothers and their full-term infants is a RCT with two parallel groups (intervention versus passive control group). The study has been designed in accordance with the SPIRIT 2013 statement (see Additional file 1 for complete checklist) [45]. Administrative information related to the trial can be obtained in Additional file 2. The project will start in April 2016. The expected total duration of the study from the start of recruitment to the last participant finishing the 1-year assessment is 20 months. The study will start with baseline measures in the last trimester of pregnancy. The intervention period will start immediately after birth and will have a duration of 5 weeks. Maternal and infant outcomes will be measured at 2 weeks, 5 weeks, 12 weeks and 1 year after birth.

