### Data-analysis

Data will be handled according to standard procedures. Demographic characteristics and study outcomes will be described for each treatment group using means and standard deviations for continuous outcomes. Proportions for categorical data will be provided. The pattern of missingness will be checked before the analyses. All measures will be controlled for outliers and checked for normality. Skewed continuous outcomes will be transformed. The level of significance (*p* -value) is set at *p* < .05 in all analyses.

We will conduct intention-to-treat analyses, in which participants are compared according to the group they were randomly assigned to regardless of participants’ compliance, including SSC protocol adherence, or withdrawal from the study, and analyses on imputed datasets based on the multiple imputation method [52]. Primary and secondary outcomes, that will be examined once, will be compared within multivariate analyses of covariance. Multilevel mixed models will be used for repeated measures. Microbiota composition will be examined with the Pearson’s moving window correlation. Microbiota diversity will be calculated with the Simpson’s reciprocal index of diversity (1/D). The Benjamini and Hochberg method will analyse differences between the SSC group and the control group. The analyses will be adjusted for potential confounding factors identified a priori (see Table 3). Structural equation models will be used to examine the mediation effect of the potential underlying mechanisms, maternal oxytocin concentrations and infant intestinal microbiota, on maternal and infant outcomes, respectively.

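### The prenatal self-report scales, including the EPDS, are completed after allocation is disclosed and SSC instruction given, so these baseline scores are open to influence by knowledge of allocation

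*Protocol article*

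**What the plan says.** The protocol article describes the visit in two places, and they agree.

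- **Pregnancy home visit.** After eligibility is reconfirmed, "informed consent is obtained by the principle investigator and mothers will fill out the medical checklist". Then: "Next, the SSC group will be informed about the group allocation". Then: "Expectant mothers in the SSC group will receive detailed instructions on SSC". General study information, logbook explanations and a communication preference follow. The closing step is "Lastly, the mother will fill out the prenatal questionnaires".
- **Randomization.** After consent and the checklist: "Hereafter, the principal investigator will open the envelope and the mothers in the SSC group will be informed about their group allocation". The same section states that neither participants nor the principal investigator are blinded.

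Three other places show how the scores are used.

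- **Study design** treats late pregnancy as baseline: "The study will start with baseline measures in the last trimester of pregnancy".
- **Table 3 (Outcomes)** lists the prenatal measures. Among them is the scale that serves as primary outcome: "The EPDS to screen for depressive symptoms [53". The STAI, PRAQ-R, PES, a worries questionnaire, the APL, the MAAS and a social support questionnaire are also marked for late pregnancy.
- **Data-analysis** states: "The analyses will be adjusted for potential confounding factors identified a priori (see Table 3".

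No section places the prenatal questionnaires before disclosure or at another visit.

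**The concern.** A baseline covariate is safe to adjust for because allocation cannot have affected it. Here that protection is missing for the subjective scales. A woman rates her mood, anxiety, worries about the baby's arrival and attachment to the unborn child after learning her arm. In the SSC arm she does so after an instruction session that controls do not receive. Controls are not actively told their arm. They can infer it, because recruitment tells all women that some will be asked for a daily contact period.

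Two things are at stake. First, a treatment effect adjusted for a score that allocation has moved no longer estimates the total effect of allocation. Second, an imbalance on these scales in the baseline table could be chance or a reaction to allocation. The trial could not separate the two, because no pre-allocation score exists.

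**Working it through.** **Step 1: order of events.** Reading the Randomization and Pregnancy home visit sections together:

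1. Consent and medical checklist (before allocation). Table 3 places the checklist at the earlier telephone call, which is also before allocation.
2. Envelope opened; SSC group told.
3. SSC group instructed.
4. Study information and logbook explanation for all.
5. Prenatal questionnaires.

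The scales at step 5 are therefore post-allocation in both arms and post-instruction in one.

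**Step 2: role in the analysis.** Table 1 lists the EPDS outcome at 2, 5 and 12 weeks and 1 year only. The prenatal EPDS is thus not an outcome time point. It stands in Table 3, to which the adjustment sentence refers.

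**Step 3: formula.** Let Δy be the SSC-minus-control difference in postnatal EPDS, Δx the same difference in prenatal EPDS, and b the within-group slope of postnatal on prenatal score, all in SD units. Then

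adjusted effect = Δy − b × Δx.

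Randomisation makes Δy an unbiased estimate of the total effect of allocation. If allocation itself moves the prenatal score by an average amount s, the adjusted estimate departs from that effect by b × s in absolute size. Lower EPDS is better. An allocation-induced fall in the SSC arm's prenatal score therefore hides benefit, and a rise exaggerates it.

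**Step 4: inputs.** The protocol gives neither b nor s, so both are assumed: b from 0.3 to 0.7 and s from 0 to 0.3 SD. The yardstick is the planned effect in Sample size calculation, f = .24. For two equal groups this is d = 2 × 0.24 = 0.48.

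**Step 5: results.** Bias in SD, with percent of d = 0.48:

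| Shift s | b = 0.3 | b = 0.5 | b = 0.7 |
|---|---|---|---|
| 0 | 0 | 0 | 0 |
| 0.05 | 0.015 (3%) | 0.025 (5%) | 0.035 (7%) |
| 0.10 | 0.03 (6%) | 0.05 (10%) | 0.07 (15%) |
| 0.20 | 0.06 (13%) | 0.10 (21%) | 0.14 (29%) |
| 0.30 | 0.09 (19%) | 0.15 (31%) | 0.21 (44%) |

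For example, 0.5 × 0.10 = 0.05 SD, and 0.05 / 0.48 = 10%. The largest cell is 0.7 × 0.30 = 0.21 SD, and 0.21 / 0.48 = 44%.

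**The case against.** The order of steps cannot be disputed, but several limits on its consequences are fair.

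- **No shift is shown.** A reader might infer that the baseline scores are contaminated. The documents show exposure to allocation knowledge, not that any answer changed. If none did, the bias is zero. This stands.
- **The cover story weakens the route.** Recruitment presents the study as one on infant sleep, feeding, contact and general health. As described, it does not single out depression as the main target, and debriefing comes at 1 year. This makes a large shift less likely. It does not exclude one, because SSC mothers know their arm and controls can work theirs out.
- **The instruction is practical.** A reader might suppose that it promotes bonding and so would raise MAAS scores directly. The section on the intervention describes duration, positioning, covering, feeding beforehand and safety, and bonding is not named as content.
- **Much of the baseline is untouched.** It would go too far to say that the baseline table cannot show comparability at all. Age, education and number of siblings are factual, the medical checklist precedes allocation, and parity is a stratification factor. Concealment at enrolment is intact, because consent comes before the envelope.
- **Adjustment for the prenatal EPDS is not stated by name.** Table 3 mixes demographics, confounders and other information. Reading the prenatal EPDS as one of the confounders is natural, but it remains an inference.

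These points limit the finding to the subjective scales and to analyses that adjust for them. They leave the order of the visit, and what it implies for those scales, unanswered.

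**Conclusion.** The point holds in limited form. As written, the prenatal EPDS and the other self-report scales are measured after disclosure, and after SSC instruction in one arm only. They cannot be treated as pre-randomisation covariates. An analysis adjusted for them carries a potential bias of slope times shift: 0 to 0.21 SD, or 0 to 44% of d = 0.48, over the assumed ranges. The direction is unknown. These figures are an illustration, and no value inside the range can be called expected.

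The conclusion rests on the natural reading that the prenatal EPDS is among the Table 3 adjustment factors. It does not call the randomisation into question, and an unadjusted intention-to-treat comparison of postnatal EPDS is free of this bias.

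**What to change.** **Women still to be enrolled.** In both the Randomization and the Pregnancy home visit sections, state this order: consent, medical checklist, all prenatal questionnaires completed and handed in, then the envelope opened, allocation disclosed and SSC instruction given. This uses the same visit and instruments and leaves the sample size unchanged.

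**Women already enrolled under the present order.** Recruitment was due to start in April 2016, with 20 months to the last 1-year assessment. Taking off 12 months of follow-up and about 1 month from the week 34–36 visit to birth leaves about 7 months for pregnancy visits, to about November 2016. The reordering may therefore come too late for many mothers or for all of them. For these mothers, state in the report that the prenatal scores are post-allocation, and give the primary EPDS effect without prenatal-score adjustment alongside the adjusted one.

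**Cost.** The unadjusted analysis loses some precision. If b is read as the prenatal–postnatal correlation at a single time point, leaving out the covariate widens the standard error by a factor of 1/√(1 − b²). This is 1/√0.91 = 1.05 at b = 0.3, 1/√0.75 = 1.15 at b = 0.5 and 1/√0.51 = 1.40 at b = 0.7. Adjustment for factual items and for parity can stay in both analyses.
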